### Study procedures

#### Baseline serology screening

A baseline serosurvey, conducted on 2000 individuals in four urban clusters, is planned based on population proportionate to size. The participants who satisfy the inclusion criteria will be selected for the serosurvey from areas within the Vellore corporation limits after obtaining written informed consent. The inclusion and exclusion criteria are detailed in the earlier section. The baseline demographic information, along with details of any clinically relevant illness in the past 1 month, will be documented. History of confirmed COVID-19 or COVID-19-like illnesses during the period of the pandemic will also be documented. A peripheral blood sample (5 mL serum) will be collected.

#### Establishment of the cohort

Based on the seroprevalence from the serosurvey, longitudinal follow-up will be initiated in the VHDSS area. A total of 1200 residents living in the densely populated wards of zones 3 and 4 of the Vellore corporation will be recruited for the longitudinal follow-up. Those subjects who agree to the specific terms of the longitudinal follow-up of 24 months will be recruited after informed consent. One member in the household will be selected using simple random sampling. Each study participant will be assigned a unique cohort ID. The final 1200 participants will be in any of the four groups based on their vaccination and infection status with no specific distribution across these four groups. The vaccination status will be obtained and recorded at the baseline and every 6 months for those who were unvaccinated at enrolment. Details of precautionary or booster doses will also be captured during the 6 monthly interview. The vaccination certificate would be verified for confirmation of details (date, type of vaccine, number of doses, etc). Upon recruitment, blood samples (15–30 mL) will be collected, processed and stored as per standard protocol. Peripheral blood mononuclear cells (PBMCs) will be isolated and stored to assess the baseline memory T cell and B cell profiles in the future.

#### Intensive follow-up phase

The first year following recruitment of the cohort would be the intensive follow-up phase during which weekly follow-up visits and saliva sampling are planned. An assigned field research assistant (FRA) will contact the study participant every week, either by telephonic or direct visit, and collect information regarding any COVID-19-like symptoms in the preceding week. The study participants will be trained to collect 2 ml of saliva in the universal sample container, early in the morning, on one designated day of the week. The participants will be asked to collect these samples as per the study protocol, prior to routine oral hygiene, and consumption of any food or drink. The samples will be collected by the FRAs and transported to the laboratory in vaccine carriers with ice packs to maintain a temperature of 4°C. The samples, once received in the laboratory, will be aliquoted in two vials. One vial will be retained at the Wellcome Trust Research Laboratory, Vellore. The other vial is sent to the National Centre for Biological Sciences, Bangalore (NCBS) for RT-PCR.

If an individual tests positive for SARS-CoV-2, the weekly salivary sample collection will be suspended for the next 90 days. The weekly contact, however, will be continued. During the weekly contact, if a subject develops symptoms, their samples will be collected. If they are RT-PCR positive within 90 days, it will be considered as re-positive. The study participants will be requested to inform the study team if they experience any clinically significant febrile or respiratory distress. Symptomatic individuals will be advised to visit CMC Hospital, Vellore and get tested by nasopharyngeal RT-PCR, as deemed necessary, after clinical examination. Clinical symptoms, response to treatment and details of treatment during hospitalisation or during home management would be recorded on the case report form (CRF) for every participant who is positive by RT-PCR.

#### Follow-up phase: second year

During the second year of the study, weekly follow-up would be through telephonic interviews. Weekly salivary samples will not be collected, and home visits will be done only for subjects with symptoms. Any incident infection will be followed up for detailed immunological testing. Once every 6 months, a blood sample (5 mL) will be collected for assessing the serostatus of the participants to identify any infection that was missed through the RT-PCR screening. Sequencing will be done on all positive samples to identify the genetic sequence of the virus at NCBS, Bangalore and help us determine which VOC was responsible for the infections and re-infections. This will include samples classified as ‘re-positives’.

#### Detailed follow-up of COVID-19 infections

All COVID-19 infections, including symptomatic and asymptomatic, will be followed up from the day of the positive report (day 0). Blood samples (30 mL) will be collected for PBMC isolation and storage within 24 hours of identification of positives on day 0, day 30 (+2 days) and day 90 (+7 days) post-infection.

### Sample collection

*Blood sample—serology*: 5 mL of peripheral blood will be collected (in serum tubes) from 2000 individuals during the baseline serosurvey, and once every 6 months from the 1200 study participants who are part of the longitudinal cohort.

*Salivary sample*: salivary samples will be self-collected, stored and transported to the NCBS laboratory, Bengaluru, as per the standard operating procedure, once a week during the first year of the study. The results will be uploaded into the secure data entry portal designed for the laboratory.

*Nasopharyngeal swab*: if any study participants report any clinically significant febrile illness or respiratory distress, they will be offered a medical consultation, and when necessary, a nasopharyngeal RT-PCR at CMC, Vellore or in any institute of their choice.

*Blood sample (for PBMC)*: 30 mL (minimum 15 mL) of blood will be collected (in 9 mL heparin tubes) after recruitment into the longitudinal study and for confirmed SARS-CoV-2 infections on day 0, day 30 and day 90. PBMCs will be separated by density gradient centrifugation method and cryopreserved in liquid nitrogen.

### Laboratory procedures

#### Weekly salivary samples

Upon receipt and aliquoting, salivary samples will be pooled for testing on the same day. Ten microlitres of five samples each will be pooled in a single well of the PCR plate, and 6 µL of proteinase K of 50 µg/µL concentration will be added to each well. Subsequently, the plates will be sealed and heated at 95°C for 5 min in a dry thermal bath. After heat inactivation, the plates will be stored at −80°C. The pooled PCR plate and an aliquot of saliva will be transported on dry ice to NCBS. RT-PCR will be performed on the pooled samples targeting the N gene, E gene and RdRp gene of SARS-CoV-2. The limit of detection of the commercial kit that is used for testing is 100 copies/mL and the sensitivity of detection in saliva samples is around 94% compared with nasopharyngeal swab.^19^ If any pool turns out to be positive, RT-PCR will be performed on individual samples. All positive samples will undergo sequencing.

### Blood samples

#### Serological assays

The plasma or serum sample collected at different time points will be tested for IgG antibody against spike protein using a high throughput automated platform (Diasorin LiaisonXL).

#### Immunophenotyping

Quantitation of SARS-CoV-2-specific T cells will be done by flow cytometric detection of cytokines and activation induced marker upregulation in T cells after stimulation with peptide pools. PBMC stimulation will be done using a 10-mer peptide pool for CD8 and 20-mer peptide-pools for CD4 T cells. Four peptide pools will be used, corresponding to the major proteins of SARS-CoV-2 (spike, envelope, membrane and nucleoprotein). For all the stimulation conditions, one well (vehicle-treated) will act as negative control. An additional well of cytomegalovirus (CMV)-peptide-stimulated control (a mix of 10-mer and 15-mer CMV peptides) will be kept as positive control for each sample. Baseline levels of cross-reactive T cells to non-SARS-CoV-2 human coronaviruses (hCoV) will be estimated using the same methodology, using peptide pools derived from hCoV strains. Memory B cells will be detected by flow cytometry after staining PBMCs with fluorophore-tagged viral proteins and memory B cell markers.

### Statistical analysis

Seroprevalence is estimated as a proportion and will be assumed to follow a binomial distribution. The incidence of infection within the cohort is expected to follow a Poisson distribution. We will permit repeated infections to be captured in analysis and account for the same in the analysis. A time-to-event analysis using Prentice, Williams and Peterson models comparing incidence in the exposed and unexposed cohorts will be performed. We will adjust for background infection rates in each cluster (ward) and covariates such as age, socioeconomic status, vaccination status, per-capita floor space and occupation class.

The statistical analysis plan will detail the estimation of seroprevalence, its risk factors, the incidence of primary and re-infection, and a comparison of these rates. Continuous variables will be described using mean (SD) and median (IQR) where necessary. Categorical data will be expressed as frequency (%). Incidence of infection and re-infection will be calculated per thousand person-years. HRs will be estimated to assess protection/risk conferred by vaccination and previous infection.

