### Objectives and expected outcomes

The CORES Study has the objectives and outcomes as described in box 1.

Box 1Objectives and outcomes of the CORES StudyObjective 1: To estimate the seroprevalence of antibodies to SARS-CoV-2 spike protein in Vellore (May–October 2021)Outcome:The proportion of individuals ≥18 years of age who are seropositive for antibodies to spike protein of SARS-CoV-2 in Vellore.Prevalence of seropositivity across clusters (wards).Objective 2: To measure the incidence of SARS-CoV-2 infection in a cohort of individuals ≥18 years in Vellore (May 2021–October 2023)Outcome:Incidence of SARS-CoV-2 infection among those without evidence of prior infection or vaccination.Incidence of SARS-CoV-2 infection among those with evidence of prior SARS-CoV-2 infection.Incidence of SARS-CoV-2 infection in those who have received at least one dose of COVID-19 vaccine at least 14 days prior to infection.Objective 3: To track cellular and humoral immune correlates of COVID-19 infection, re-infection and clinically significant disease (May 2021–October 2023)Outcome:Kinetics and longevity of antibody responses and immunological memory.Influence of baseline memory T and B levels (both SARS-CoV-2 specific as well as cross-reactive) on infection.

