### Inclusion and exclusion criteria

Inclusion criteria:

Age 18 years and above.Permanent residents of the selected wards.Only one member from each selected household will be enrolled.Individuals with a history of clinical illness suggestive of COVID-19 or confirmed COVID-19 in the past, who are seropositive at baseline in the serosurvey (symptomatic seropositive).Individuals seropositive at baseline, with no history of COVID-19 (asymptomatic seropositive).Individuals seronegative at baseline, stratified by the ward of residence.

Exclusion criteria:

Participant refusal of consent.Pregnant women and immunocompromised patients.Participants not willing for follow-up until the end of the study.Active cancers or bleeding disorders.

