### Statistical considerations

#### Assumptions

We make the following assumptions. The assumptions were based on the early findings of the Com-CoV study as there were no published data regarding vaccine efficacy and re-infections prior to the start of the study.^18^

Fifty per cent of the population will be seropositive at baseline.Forty per cent will have received two doses of vaccine mid-way into the study.The annual incidence of SARS-CoV-2 infection detected by the salivary PCR in those unvaccinated and have no detectable antibodies (unexposed) at baseline will be 12%.The annual incidence of SARS-CoV-2 infection detected by the salivary PCR in those vaccinated and unexposed at baseline will be 6% (Vaccine Effectiveness (VE) 50% against infection).The annual incidence of SARS-CoV-2 infection detected by the salivary PCR in those unvaccinated and who have antibodies (exposed) at baseline will be 4.8%.The annual incidence of SARS-CoV-2 infection detected by the salivary PCR in those vaccinated and exposed at baseline will be 4%.

Based on these assumptions, for 90% power to detect a 5% difference in the rate of re-infection and primary infection in the cohort, a sample size of 1200 participants is proposed, after allowing for a 10% dropout rate.

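### The binomial assumption for seroprevalence does not match the clustered serosurvey, so a plain binomial interval is likely too narrow, by an amount the article does not let one fix

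*Protocol article*

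**What the plan says.** The Statistical analysis section states: "Seroprevalence is estimated as a proportion and will be assumed to follow a binomial distribution". It names no design effect, weight or cluster-based variance for this estimate. Its adjustment for background infection rates by cluster (ward) comes directly after the time-to-event model for incidence. The section also says that the statistical analysis plan, which is not shown, will detail how seroprevalence is estimated.

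The survey itself is described elsewhere:

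- Baseline serology screening: the survey is "conducted on 2000 individuals in four urban clusters, is planned based on population proportionate to size". It adds: "The participants who satisfy the inclusion criteria will be selected for the serosurvey from areas within the Vellore corporation limits".
- Inclusion and exclusion criteria, which therefore apply to the survey: participants must live permanently in the selected wards, and "Only one member from each selected household will be enrolled".
- Establishment of the cohort: "One member in the household will be selected using simple random sampling". This is written for the cohort, not for the serosurvey.
- Box 1, Objective 1: the target is the proportion of adults in Vellore who are seropositive. A second outcome is "Prevalence of seropositivity across clusters (wards").
- Study setting: the city has 4 zones and 60 wards.
- Assumptions: "Fifty per cent of the population will be seropositive at baseline".

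**The concern.** A binomial model for the total number of positives treats the 2000 people as independent and equally likely to be chosen. People who live in the same area share exposure and access to vaccination, so their serostatus is likely to be correlated. Objective 1 makes prevalence by ward an outcome in its own right. With hundreds of people per cluster, even a weak correlation removes much of the information that 2000 independent people would give. If the sentence is followed as written, the Objective 1 result would carry an interval that overstates its precision for Vellore.

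The household rule raises a different question. If one adult is drawn at random per household, each adult's chance of selection is 1 divided by the number of eligible adults there. Choosing areas in proportion to population does not correct this. It bears on the point estimate rather than on the width of the interval.

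**Working it through.** **Inputs.** From the article: n = 2000, four clusters, expected prevalence 50%. The average cluster size is 2000/4 = 500; equal sizes are assumed. The article gives no target precision, ICC or design effect for the serosurvey, so there is no published figure to reproduce. ICC values, the number of wards and household sizes below are assumptions.

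**Step 1, binomial interval.** Half-width = 1.96 × √(0.5 × 0.5 / 2000) = 1.96 × 0.01118 = 0.0219, or ±2.2 points.

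**Step 2, four sampled clusters.** Design effect (DE) = 1 + (m − 1) × ICC with m = 500. The interval widens by √DE, and effective n = 2000/DE.

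| ICC (assumed) | DE | √DE | Half-width (points) | Effective n |
|---|---|---|---|---|
| 0.001 | 1.50 | 1.22 | ±2.7 | 1334 |
| 0.005 | 3.50 | 1.87 | ±4.1 | 572 |
| 0.01 | 5.99 | 2.45 | ±5.4 | 334 |
| 0.02 | 10.98 | 3.31 | ±7.3 | 182 |
| 0.05 | 25.95 | 5.09 | ±11.2 | 77 |

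The interval doubles when DE = 4, that is at ICC = 3/499 = 0.006. These rows use the normal multiplier. A variance estimated from four clusters has 3 degrees of freedom, with multiplier 3.18 in place of 1.96, a further factor of 1.62. The ratios to the binomial interval then run from 1.99 (ICC 0.001) to 8.27 (ICC 0.05).

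**Step 3, wards as the sampled units.** The number of wards sampled is not given.

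- About 30 wards (assumed), m ≈ 67: DE = 1 + 66 × 0.01 = 1.66 and 1 + 66 × 0.02 = 2.32. √DE = 1.29 and 1.52, so the half-width is ±2.8 to ±3.3 points.
- 20 wards (assumed), m = 100: DE = 1.99 and 2.98 at the same ICCs. √DE = 1.41 and 1.73, so the half-width is ±3.1 to ±3.8 points.

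**Step 4, the four clusters as strata.** If they are the four zones, all included, differences between them add nothing to the sampling variance. Variance from selecting wards within zones would remain, as in step 3.

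**Step 5, one adult per household.** Weights equal the number of eligible adults, k. The Kish factor for interval width is √(E[k²]/E[k]²). With linear change in prevalence by household size, the unweighted estimate is off by slope × (E[k²]/E[k] − E[k]). The assumed slopes are 2 and 4 points per extra adult, which is 10 and 20 points from one to six adults.

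| Assumed share of households by number of adults | E[k] | E[k²] | Width factor | Shift at slope 2 / 4 |
|---|---|---|---|---|
| 2: 60%, 3: 20%, 4: 20% | 2.60 | 7.40 | √1.095 = 1.05 | 0.5 / 1.0 points |
| 1: 10%, 2: 40%, 3: 25%, 4: 15%, 5: 10% | 2.75 | 8.85 | √1.170 = 1.08 | 0.9 / 1.9 points |
| 1: 20%, 2: 40%, 3: 20%, 4: 10%, 6: 10% | 2.60 | 8.80 | √1.302 = 1.14 | 1.6 / 3.1 points |

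With no gradient by household size the shift is zero.

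**The case against.** Three arguments carry weight.

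First, the article leaves the detail of seroprevalence estimation to an analysis plan that is not shown, and variance estimators and weights are normal content there. A design-based variance cannot be ruled out. This lowers the certainty. It does not remove the mismatch, because the distributional assumption is stated in the article: a plan that followed it literally would understate the error, and one that used a design-based variance would depart from it.

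Second, binomial may only name the type of outcome, as Poisson does for incidence in the next sentence, and a cluster-robust or random-effects analysis can start from a binomial outcome. That is a fair reading. Even so, the text stops there for seroprevalence and brings in clusters only after the incidence model.

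Third, the size depends on facts the article does not settle. Cluster means one of four urban areas in the serosurvey section but a ward in Box 1 and in the analysis section, and the city happens to have exactly four zones. The surveillance area is also called largely homogeneous, although that describes its social make-up and not its seroprevalence.

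This third argument stands against a reading that a reader might infer: that the interval is, as a fact, several times too narrow. That needs both four sampled clusters and an ICC above about 0.006 (normal multiplier), and the documents establish neither. A reader might also take the one-member rule as a cause of the narrow interval. It is not: it removes within-household correlation, and its weighting effect on width is small.

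**Conclusion.** The binomial sentence does not fit the survey design, and a plain binomial interval of ±2.2 points is likely too narrow for a claim about Vellore. The factor is about 1.2 to 5 if four clusters of 500 were sampled (assumed ICC 0.001 to 0.05, normal multiplier). It is about 1.3 to 1.5 if roughly 30 wards were sampled (assumed number, assumed ICC 0.01 to 0.02). The four clusters contribute nothing between them if they are zones used as strata. The documents do not decide among these cases.

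Unequal selection within households is a separate and conditional point. It applies if the random choice of one member, stated for the cohort, was also used in the serosurvey. It biases the estimate only if seroprevalence varies with household size. The documents do not support saying that the estimate is in fact pulled towards small households by a known amount; the shifts of 0.5 to 3.1 points above are illustrations. The effect on width is a factor of 1.05 to 1.14 under the assumed household sizes.

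**What to change.** - State what the four urban clusters are, how they and the wards were selected, and use the word cluster for one unit throughout Box 1, the serosurvey section and the analysis section.
- Replace the binomial sentence with a design-based estimate. Its variance should be taken at the level of the units actually sampled: wards where wards were selected, with the four zones as strata if that is what they are, and degrees of freedom to match.
- Weight by the number of eligible adults in the household if one was chosen at random, and say how that choice was made in the serosurvey.
- Alternatively, restrict the Objective 1 claim to the sampled areas.
- Post-stratify to the demographic surveillance population only if the claim is limited to zones 3 and 4. Study setting says the system covers 120 000 people there, out of close to 500 000 in the city, so weighting to it could move an estimate for Vellore away from its target.

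The cost is protocol and analysis plan wording, survey-analysis code, and the count of eligible adults for each surveyed household if it was not recorded. The downside is a wider interval and, if only four clusters were truly sampled, a variance estimate that is itself imprecise on 3 degrees of freedom.

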### Key comparisons in the study

We will make comparisons between:

Incidence rates of infection overall and in seropositive and seronegative subgroups.Incidence rates of infection among the vaccinated individuals in the cohorts.Kinetics and longevity of memory B and T cells in infections occurring in the seropositive and seronegative cohort.Baseline cross-reactive T cells and antibodies to non-SARS-CoV-2 β-CoV between symptomatic infections versus asymptomatic infections versus uninfected individuals in the seronegative cohort.Baseline SARS-CoV-2-specific memory T and B cells and antibody levels between infected individuals versus uninfected individuals in the seropositive cohort.

### Data management plan

All the CRFs will be in the electronic format (REDCap), and the entry platform will be connected to the central database server. The data management system is responsible for the periodical validation process and quality of the data. Any further correction in the database after the entry is ‘saved’ is accompanied by a duly completed ‘data clarification form’. The electronic data management system tracks key study progress parameters on an access-restricted online dashboard. The weekly contact made by the FRAs will be independently validated by a field worker who calls 5% of all individuals who were contacted that week.

### Ethics and dissemination

The study has been approved by the Institutional Review Board (IRB No: 13585) of CMC, Vellore. The study will adhere to the principles that govern biomedical research involving human subjects as required in India. The Declaration of Helsinki will be followed to assure that the rights, integrity and confidentiality of study participants are protected, and that reported results are credible and accurate. The privacy and confidentiality of all information collected, including those derived from clinical specimens, will be ensured during and after the project. Individuals will not be identified in any reports or publications based on the study. All participant data will be computerised using password protection. The participants will be asked to provide written informed consent. The knowledge gained and the results will be made available through journal publications and conference presentations.

